### 5.2. Secondary Outcomes

The following parameters will also be analyzed:-Duration of hospitalization.-Weight gain (percentage increase from birth to discharge).-Length of antibiotic therapy.-Incidence of other infectious or inflammatory complications.

The collected biological material will also enable the exploratory analysis of microbiota composition and its changes throughout the experiment.

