### 2.3. Participants, Enrollment, Randomization, and Statistical Methods

The studied population will be the group of premature newborns (born between 24 0/7 and 36 6/7) who are at increased risk of developing NEC and who may benefit most from FMT.

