#### 2.3.3. Statistical Analysis

All analyses will be conducted on an intention-to-treat basis.

The primary endpoint is safety, defined as the incidence of adverse events (AEs) and serious adverse events (SAEs) during the observation period.

The proportion of patients experiencing at least one AE or SAE will be compared between groups using Fisher’s exact test. The chi-square test will be applied when its assumptions are met.

The incidence of specific AEs will also be compared using Fisher’s exact test. Relative risks (RRs) with two-sided 95% confidence intervals (CIs) will be calculated.

If the number of events per patient is analyzed, between-group comparisons will be performed using Poisson regression or negative binomial regression, depending on data dispersion.

Time to first AE, if applicable, will be analyzed using Kaplan–Meier estimates and compared using the log-rank test.

Continuous variables will be assessed for normality using the ShapiroWilk test. Normally distributed variables will be compared using Student’s *t*-test, and non-normally distributed variables using the Mann–Whitney U test.

Two-sided tests will be used throughout, with statistical significance set at α = 0.05. Estimates will be presented with two-sided 95% confidence intervals. Analyses will be performed using validated statistical software (e.g., R, Stata, or SAS); the exact software and version will be documented in the final report.

Given the limited sample size, the study is not powered for formal hypothesis testing of small effect sizes. Therefore, interpretation will focus primarily on effect size estimates and their 95% confidence intervals rather than solely on statistical significance. Clinically meaningful differences will be considered in the context of effect magnitude and precision.

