## 4. Detailed Procedure

### 4.1. Transplant Recipients Procedures

FMT will be administered to patients in the study group who meet the inclusion criteria and do not meet the exclusion criteria, in the form of a deep rectal infusion, in a volume of 5 mL, twice at 6 h intervals, between 3 and 6 days after birth and/or up to 14 days in patients who experience temporary contraindications to the use of FMT or in patients who will be transferred to our center for treatment from an external facility.

In the first phase of the experiment, 10 patients from the study group born between 28 0/7 and 36 6/7 will undergo the procedure. All adverse effects of the therapy will be monitored and documented on an ongoing basis. If no serious adverse events (SAEs) occur, we will include another 10 patients born between 24 0/7 and 27 6/7 in the study (phase two of the experiment).

A serious adverse event (SAE) is defined as any medical event that, at any dose, meets at least one of the following criteria:Leads to death.Is life-threatening to the participant.Requires hospitalization or prolongs hospitalization.Leads to permanent or significant impairment of function or disability.A detailed description of the monitored parameters is provided below.

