### 4.4. Procedures for the Patients in the Control Group

Check whether the patient meets the inclusion criteria for the experiment.Check whether the patient meets the exclusion criteria.Discuss the purpose and procedures of the experiment with the patient’s parents/guardians and obtain their informed consent for the child’s participation in the experiment. This includes consent for the processing of personal data and the use of biological material samples for scientific purposes, as well as consent for participation in surveys and follow-up on the effectiveness of therapy.Collect blood parameters indicating inflammation (leukocytosis, CRP, procalcitonin) at the “0” point (“BEFORE intervention”), between signing the consent form and the fifth day of the child’s life.Ensure that biological material samples (feces, urine and blood samples) are collected before (point “0”) FMT, as described in the section below, or collect samples before the sixth day of the child’s life.For the control group, the matching time point for administering gut microbiota doses and counting “post” days is assumed to be the sixth day of the child’s life.From day 6 (the matching time point), any adverse events or deviations from the norm will be recorded, such as deterioration in general condition, appearance of symptoms of infection or increase in inflammation indicators.Blood inflammation parameters (leukocytosis, C-reactive protein (CRP), procalcitonin) will be collected during the “post-matching time point” period at least once within 72 h of day 6, or more frequently if the patient’s clinical condition requires it, as assessed by the attending physician.

The following will also be recorded in both study groups:-The number of days spent in hospital;-Percentage increase in body weight (birth weight vs. weight at discharge);-The number of days of antibiotic therapy received during hospitalization (monitoring until discharge from the hospital conducting the experiment).

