### 5.3. Feasibility and Missing Data Management

Most biological samples will be collected during routine hospitalization, which in this population typically extends for several weeks. Therefore, the majority of scheduled collections will overlap with standard clinical monitoring.

Based on institutional experience, we anticipate an attrition rate of approximately 15%. For safety endpoints, no imputation of missing data will be performed. Analyses will be based on available data. The extent and reasons for missing data will be reported descriptively. Sensitivity analyses may be conducted if the proportion of missing data exceeds 10%.

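### Weight gain as percentage increase from birth to discharge is not scaled for time, so a longer, complicated stay can look like better growth

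*Protocol article*

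**What the plan says.** Section 5.2 of the protocol article lists "Weight gain (percentage increase from birth to discharge" as a secondary outcome. Section 4.4 repeats it among the items recorded in both groups: "Percentage increase in body weight (birth weight vs. weight at discharge". Neither place gives a fixed age, a per-day or per-kilogram scale, or a z-score.

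Length of stay is an outcome in its own right, listed as "Duration of hospitalization" in section 5.2 and recorded as "The number of days spent in hospital" in section 4.4. Section 4.1 includes "Requires hospitalization or prolongs hospitalization" among the SAE criteria.

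For continuous variables, section 2.3.3 names Student's t-test where normality holds and "non-normally distributed variables using the Mann–Whitney U test" otherwise. It states no adjustment for stay or gestational age.

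**The concern.** A growth measure compared between groups should cover the same time in each infant or be divided by the time covered. This one does neither. Its clock stops at discharge, which follows treatment and can be delayed by the harms the study sets out to detect. An event that counts as harm under section 4.1 because it prolongs the stay therefore also gives the infant more days in which to gain weight.

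The eligible range of 24 0/7 to 36 6/7 weeks adds a second source of variation in stay. Adjusting for gestation would deal with part of that, but not with longer stay caused by complications within a gestational band.

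At stake is the sign of an estimate. Section 2.3.3 says interpretation will rest mainly on effect estimates and their intervals, and section 2.3.1 says the pilot is meant to inform a later randomized trial. A weight-gain difference that can favour the group with more complications would be a poor input to that design.

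**Working it through.** **Inputs.** The article states no expected gain, standard deviation, growth rate or power for this outcome, so there is no figure to reproduce. On stay it says only "routine hospitalization, which in this population typically extends for several weeks". The following are assumptions for illustration:

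- growth velocity g = 15 g/kg/day, range 10 to 20;
- discharge at day D = 42 or D = 56;
- exponential growth starting at day r, with r = 0 (no early weight loss) or r = 10 (birth weight regained only at day 10).

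**Step 1. Effect of stay alone.** Percent gain = 100 × (exp(g × (D − r)/1000) − 1).

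| g | r | D = 42 | D = 56 | Difference |
|---|---|---|---|---|
| 10 | 0 | exp(0.42) − 1 = 52% | exp(0.56) − 1 = 75% | 23 points |
| 15 | 0 | exp(0.63) − 1 = 88% | exp(0.84) − 1 = 132% | 44 points |
| 20 | 0 | exp(0.84) − 1 = 132% | exp(1.12) − 1 = 206% | 75 points (from unrounded values) |
| 15 | 10 | exp(0.48) − 1 = 62% | exp(0.69) − 1 = 99% | 38 points |

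**Step 2. Can a slower-growing infant score higher?** Compare 12 g/kg/day to day 56 with 15 g/kg/day to day 42.

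- r = 0: exp(0.672) − 1 = 96% against 88%.
- r = 10: exp(0.552) − 1 = 74% against 62%.

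In both cases the infant growing 20% more slowly scores higher.

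**Step 3. How much slowing offsets 14 extra days?** Scores are equal when g₂ = g₁ × (42 − r)/(56 − r).

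- r = 0: 15 × 42/56 = 11.25 g/kg/day, a slowing of 25%.
- r = 10: 15 × 32/46 = 10.4 g/kg/day, a slowing of about 30%.

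With less slowing the measure ranks the two infants wrongly; with more, it ranks them correctly.

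**Step 4. Group level.** A simulation took 20 infants per group, stay with mean 45 and SD 15 days, velocity with mean 15 and SD 2 g/kg/day, r = 10, and a complicated course in 60% of one group and 30% of the other. All of these are assumptions except the group size.

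- Complications adding 21 days and slowing growth by 20%: mean percent gain is about 8 points higher in the more complicated group, although its mean velocity is 0.9 g/kg/day lower. The difference favours that group in about 70% of simulated trials.
- Complications adding 14 days and slowing growth by 30%: the mean difference is −1.4 points, which is slightly in the right direction.

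**Step 5. Does a velocity do better?** Velocity = 1000 × ln(discharge weight/birth weight)/age at discharge. With r = 10, the two infants of step 2 score 15 × 32/42 = 11.4 and 12 × 46/56 = 9.9 g/kg/day, which is the correct order. Some dependence on stay remains. Two infants both truly growing at 15 g/kg/day and discharged at days 40 and 61 score 15 × 30/40 = 11.3 and 15 × 51/61 = 12.5. For discharge at days 42 and 56, the slowing that velocity fails to detect is 1 − (32/42) × (56/46) = 7%, against about 30% for the percentage.

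**The case against.** A reader might infer that harm which lengthens stay always moves this outcome in the favourable direction, or that the outcome reflects stay rather than growth. The documents do not support either reading. Complications can also slow growth, and the two effects oppose each other: step 3 gives the break-even, and the second scenario of step 4 lies just beyond it. In the formula, velocity and days enter as a product, so growth counts as much as time. The article gives no data on how far complications lengthen stay or slow growth, so the direction is a possibility to guard against and not a prediction.

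The illustration also rests on chosen stays and growth rates. That is fair. The day-10 delay cuts the gap from 44 to 38 points and leaves the ranking error in place.

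The article has safeguards as well. Stay is reported beside weight gain. Section 2.3.3 plays down significance testing, and section 5.4 warns against causal reading of group differences. These help a careful reader, but none of them corrects the estimate. A fuller analysis plan might add adjustment for gestation. It would still be analysing the definition that the article states twice. Adjusting for stay itself would mean conditioning on a post-treatment outcome.

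Finally, the outcome is secondary, the study has 20 infants per group with no power calculation, and no stated progression or stopping rule uses weight gain. This stands in full and limits the weight of the point.

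**Conclusion.** The concern holds as a fault in a stated outcome definition. Percentage gain to discharge mixes growth rate with a time span that treatment-related complications can lengthen, so a group with more complications can appear to grow better. Under the assumed 15 g/kg/day and a 42-day stay, two extra weeks are worth about 38 to 44 points, and slowing of up to 25% to 30% would be hidden or reversed. These sizes depend on growth rates and stays that the article does not give. The dependence on stay itself does not: it holds at any positive growth rate. The change is worth making, but the primary safety comparison and the decision to open the second phase are unaffected.

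**What to change.** In sections 4.4 and 5.2, make the compared outcome growth velocity in g/kg/day, calculated as 1000 × ln(discharge weight/birth weight)/age at discharge in days. Compare the groups with adjustment for gestational age band (24 0/7 to 27 6/7, and 28 0/7 to 36 6/7 weeks). Keep the percentage increase as a descriptive item only.

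The denominator should be age at discharge and not days in the study hospital. Section 2.3.4 admits infants transferred from elsewhere at up to 14 days of age, and for them the study-hospital stay is shorter than the birth-to-discharge interval over which the weight was gained, so velocity would be overstated.

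The cost is a short change of definition. Both weights are already recorded. Age at discharge is not listed as an item, but it follows from the dates of birth and discharge.

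The limitation to state is the small residual dependence on stay caused by early weight loss (step 5). Where a weight at a fixed age is available, change in weight z-score from birth to that age avoids it, but this needs a reference chart, the infant's sex and gestational age, and a weight taken at that age. A z-score change measured to discharge would keep the same outcome-dependent end point.

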### 5.3. Feasibility and Missing Data Management

Most biological samples will be collected during routine hospitalization, which in this population typically extends for several weeks. Therefore, the majority of scheduled collections will overlap with standard clinical monitoring.

Based on institutional experience, we anticipate an attrition rate of approximately 15%. For safety endpoints, no imputation of missing data will be performed. Analyses will be based on available data. The extent and reasons for missing data will be reported descriptively. Sensitivity analyses may be conducted if the proportion of missing data exceeds 10%.

### 5.4. Discussion

For many years, necrotizing enterocolitis has been associated with high and stable mortality rates, as well as severe complications. Despite significant progress in neonatal care, diagnosing and treating this condition remains a major clinical challenge. The available treatments are often ineffective and have side effects. Based on available studies, it is becoming increasingly clear that disturbances in gut microbiome composition play a very important role in the pathogenesis of NEC. The promising approach of restoring microbial balance using FMT could be beneficial in preterm infants at risk of NEC. Consistent experimental research shows reduced NEC incidence and reduced inflammation parameters following FMT. Although large-scale trials remain unavailable, early clinical studies suggest favorable safety, even among heavily immunosuppressed adult patients [31].

At the same time, meta-analyses do not provide clear evidence supporting the preventive effect of standardized probiotics against NEC. Although strains of Bifidobacterium and Lactobacillus may have beneficial effects, they appear insufficient to restore the natural microbiota, particularly in the context of multifactorial dysbiosis [12,13,14].

Despite numerous studies and meta-analyses evaluating probiotics in reducing NEC-related mortality and morbidity in preterm infants, ESPGHAN and AAP recommendations remain cautious. An optimal strain, dose, or combination for routine supplementation has not yet been clearly established [15,16,17,18].

We hope that this study will generate essential safety data to inform future randomized controlled trials assessing prophylactic efficacy and potential long-term benefits of FMT.

We acknowledge several important limitations of this study.

First, the open-label design may introduce detection bias, particularly for subjective safety endpoints such as feeding intolerance. Although objective definitions for sepsis and NEC (Bell’s criteria, CRP levels, blood cultures) are applied to mitigate this risk, complete elimination of assessment bias cannot be ensured.

Second, the non-randomized allocation of participants may introduce selection bias and residual confounding. Despite applying identical inclusion and exclusion criteria and conducting parallel observation in both groups, unmeasured baseline differences may influence observed safety outcomes. Therefore, causal inferences regarding between-group differences should be interpreted with caution.

Third, the relatively small sample size (20 participants per group) limits statistical power and increases the likelihood of type II error. The study is not powered to detect small or moderate differences in safety outcomes, and confidence intervals may be wide. Consequently, non-significant findings should not be interpreted as evidence of the absence of effect. The primary aim of this investigation is to generate preliminary safety data and identify potential safety signals to inform the design of future adequately powered randomized controlled trials.

Despite these limitations, the prospective design, standardized GMP-based FMT preparation, and structured safety monitoring strengthen the internal consistency of the study. We anticipate that the findings will provide essential groundwork for subsequent randomized efficacy trials.

## Figures and Tables

**Table 1 pharmaceuticals-19-00437-t001:** Time windows for biological sample collection points.

Sampling Point	Sampling Time	Time Window ***
PRE (point “0”)	First stool after birth *	before administration of the first dose of microbiota (FMT1)
POST7	7 days after FMT2 ** 13th day of life (control group)	±3 days ***
POST14	14 days after FMT2 ** 20th day of life (control group)	±3 days ***
POST30	30 days after FMT2 ** 36th day of life (control group)	±7 days ***
POST60	60 days after FMT2 ** 66th day of life (control group)	±7 days ***
POST120	120 days after FMT2 ** 126th day of life (control group)	±14 days ***

* For preterm infants transported from other hospitals, the PRE stool sample should be obtained from the first stool passed after obtaining parental/guardian consent. ** For the intervention group, counting of “POST” days begins on day 1 after FMT1 administration (matching day). For the control group, counting begins from the infant’s chronological age: POST7 = 6th day + 7 days = 13th day of life, POST14 = 6th day + 14 days = 20th day of life, POST30 = 6th day + 30 days = 36th day of life, POST60 = 6th day + 60 days = 66th day of life, and POST120 = 6th day + 120 days = 126th day of life. *** Samples should be collected within the indicated time windows. If collection is not possible within the window, samples should be collected at the nearest possible time, and deviations must be documented.

## Data Availability

Data generated during this study will be publicly available upon publication of the results.
